### Calculation of sample size

2.1

To achieve an effect size = 0.40 between two groups (conventional treatment and PDT), for the difference in the amount of bacteria present in the crevicular fluid of participantstreated with scaling and those treated with PDT, assuming a type 1 error of 0.2^[1]^ and 95% confidence level, the total sample size will be 34 participantsdistributed into 2 groups. The sample calculation was performed in Excel, based on the calculation formula described by Kadam and Bhalerao. Considering a 20% drop-out, 3 extra participantswill be inserted into each group, if there is said drop-out this will provide a final sample of participants per group.^[32]^

To ensure participants’ adherence to the research, the steps will preferably coincide with the participants's return visits to their routine orthodontic appliance maintenance. Participants uptake will occur during routine consultations with the orthodontist.

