### Randomization

2.5

To randomly distribute the participants into the experimental groups, a 40-lot draw will be made using the Microsoft Excel program, version 2017. The distribution of groups will be identical (1: 1) for the two groups. The distribution will be done in a blocking fashion (8 groups of 5 patients). Opaque envelopes will be identified with sequential numbers (1 to 40) and there will be information about the corresponding experimental group in the order obtained in the draw. The envelopes will be sealed and will remain sealed in numerical order until the start of the periodontal treatments. The drawing and preparation of the envelopes will be performed by a person not involved in the study. Immediately prior to periodontal treatment the investigator responsible for treatment will open 1 envelope (without changing the numerical sequence) and perform the indicated procedure. Three additional patients will be included in each group in view of the dropout predicted in any clinical study (considering a dropout of 20%).

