### Experimental design

2.10

Immediately prior to periodontal treatment, the investigator will remove and open 1 envelope (without changing the numerical sequence of the other envelopes) and perform the indicated procedure. In this manner, the 34 patients will be allocated into the experimental or control groups, as follows:

**G1**- Control group (n = 17) - patients will receive scaling and oral hygiene guidance + application of placebo PDT.

**G2**- Experimental group (n = 17) - patients will be treated with scaling and oral hygiene guidance + PDT application. Photodynamic therapy will be performed at 8 sites with gingival hyperplasia (pseudopocket).

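### Three extra patients per group cover a 15% drop-out, not the stated 20%: 20 randomised per group are expected to leave 16 completers, one short of the planned 17

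*Protocol article*

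**What the plan says.** Section 2.1 of the protocol article gives the calculated size: "the total sample size will be 34 participantsdistributed into 2 groups". The abstract and section 2.10 put this at 17 in each group. Section 2.1 then adds the allowance, "Considering a 20% drop-out, 3 extra participantswill be inserted into each group", and gives its purpose: "if there is said drop-out this will provide a final sample of participants per group". The number of completers that belongs in that last clause does not appear in the text.

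Section 2.5 states the allowance again, with the same 20% rate: "Three additional patients will be included in each group in view of the dropout predicted in any clinical study". It fixes the number to be randomised, "a 40-lot draw will be made using the Microsoft Excel program", and the ratio, "The distribution of groups will be identical (1: 1) for the two groups". The plan is therefore 20 per group and 40 in total, which is 34 plus twice 3.

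Section 2.15 limits the analysis to patients who completed the study. Sections 2.3 and 2.11 also take patients out after enrolment, for example when they start a listed medicine, become pregnant or report using mouthwash. No section provides for replacing patients who are lost, beyond the three extra per group.

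**The concern.** The allowance looks like 20% of the 17 completers wanted (3.4), rounded down to 3. A drop-out rate applies to the patients who start, not to those who finish, so the needed number is divided by the retention rate. Multiplying the target by 1.20 always gives too few, and rounding down adds to the shortfall.

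At stake is whether the analysed sample reaches the size the protocol sets. With a completers-only analysis, every withdrawal or later exclusion comes straight off that sample, and these three patients per group are the only margin. This point is separate from the conflict between the 34 patients allocated in section 2.10 and the 40 envelopes in section 2.5. Even the larger figure, 40, does not absorb the drop-out rate given for it.

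**Working it through.** **Inputs, all from the protocol article**
- Target: 17 per group, 34 in total (abstract, 2.1, 2.10).
- Drop-out rate: d = 0.20 (2.1, 2.5).
- Allowance: 3 per group (2.1, 2.5), so 17 + 3 = 20 per group.
- Lots drawn: 40, allocated 1:1 (2.5).
- Analysis set: completers only (2.15).

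**Reproducing the plan's figure.** Inflating the target by 1 + d gives 17 × 1.20 = 20.4 per group and 34 × 1.20 = 40.8 in total. The plan's 20 and 40 come out only if these are rounded down.

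**Forward check.** Completers = randomised × (1 − d).
- Per group: 20 × 0.80 = 16.
- In total: 40 × 0.80 = 32.

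That is one short of 17 per group and two short of 34.

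**What three extra patients cover.** 20 randomised still yield 17 when 3 are lost, and 3/20 = 15%. The figure 3/17 = 17.6% uses the wrong base and is still below 20%.

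**The number that matches 20%.** n/(1 − d) = 17/0.80 = 21.25, rounded up to 22 per group, 44 in total. Check: 21 × 0.80 = 16.8, too few; 22 × 0.80 = 17.6, enough.

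**Chance of reaching 17.** This assumes that each patient drops out independently with probability 0.20. For 20 randomised, the probabilities of 17, 18, 19 and 20 completers are 0.205, 0.137, 0.058 and 0.012, which sum to 0.41. Both groups reach 17 with probability 0.41² = 0.17. With 22 randomised, the figures are 0.73 for one group and 0.73² ≈ 0.54 for both.

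**Cost in power** (normal approximation, two-sided 5%). The standardised difference for which 17 per group gives 80% power is (1.960 + 0.842) × √(2/17) ≈ 0.96. At 0.96, power is 79.9% with 17 per group and 77.5% with 16, a loss of about 2.4 points. The effect of 0.96 is an assumption made for this check; the protocol does not state it. At a standardised difference of 0.40, power is 21.4% with 17 and 20.4% with 16.

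**The other reading of 34.** If 34 already contained the extra patients, the target would be 14 per group. Then 17 × 0.80 = 13.6 also falls short, and the 40 lots would have no explanation.

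**The case against.** The strongest objection is that the completer target is inferred. The clause in section 2.1 that should give it has no number, and the gap may have arisen when the text was extracted. Section 2.5 says only that three are added in view of 20% drop-out, and section 2.15 sets no minimum. This is fair as far as it goes. But 17 per group is the only target the document gives, and the 40 lots equal 34 plus 6. If the missing number were 16, it would contradict the 34.

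The second objection concerns weight. The loss is one expected completer per group and changes no test, estimand or bias. The target itself is weakly founded: the standard two-mean calculations tried with an effect size of 0.40 do not give 17 per group, and section 2.1 pairs a type 1 error of 0.2 with 95% confidence. Restoring 17 completers would therefore not restore any demonstrated power. This stands, and it limits how much the point matters. It does not make the stated allowance correct.

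The third is that probabilities of 0.41 and 0.17 sound alarming because they count 16 completers as failure, and 22 per group would itself succeed in both groups only about 54% of the time. That is also fair. The expected count, 16 against 17, is the better measure of size.

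**Conclusion.** The concern holds. Three extra patients per group do not absorb a 20% drop-out from a target of 17; they absorb 15%. At the protocol's own rate the expected analysis set is 16 per group, 32 in total, against 17 and 34. The arithmetic uses only printed figures. The one inference is that 17 is the number meant to remain after drop-out.

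The error is real and small. It should be corrected because it is stated twice and the analysis has no other protection against losses, but it does not by itself threaten the trial. Correcting it does not settle the separate questions about how 17 was derived.

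**What to change.** In sections 2.1 and 2.5, state that 20 randomised per group allow for 15% drop-out, and that at 20% drop-out 16 per group (32 in total) are expected to complete. In section 2.1, put the completer number into the clause that now lacks it. The cost is two sentences and a slightly less favourable stated allowance. Recruitment, envelopes and analysis are unchanged.

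If the claim of 17 completers at 20% drop-out is kept instead, the figure that matches it is 22 per group, 44 in total. That is more than a wording change. The 40-lot draw, the envelopes numbered 1 to 40 and the 8 blocks of 5 in section 2.5 would all have to be redone, and 44 is not a multiple of 5. The rewording is enough to make the document correct.

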### Description of the sample

2.2

The sample will be composed of healthy participants being treated with a fixed orthodontic appliance for at least 12 months and who present with gingivitis (GI greater than 10%, probing depth ≤ 3 mm from the distance from the ECJ line to the bottom of the periodontal pocket, pseudopockets will be included in the study). We will also consider the clinical signs of gingival inflammation: edema (loss of sharp gingival margin, blunting of the papillae and hyperplasia), erythema and probing discomfort. Relevant patient complaints will be considered to begin the anamnesis: gingival bleeding (metallic taste / altered taste), pain, halitosis and difficulties when eating.^[13]^

### Inclusion / exclusion criteria

2.3

To be included: healthy participants (negative medical history), of both genders, aged 10 to 30 years, with gingivitis induced by dental biofilm, predisposed by the use of a fixed orthodontic appliance, according to the classification of 2018.^[33]^

To be excluded: participants with maxillary and mandibular deformities, periodontitis, oral lesions and who have used antibiotics for less than 3 months, those who have used non-steroidal anti-inflammatory drugs and continuous corticosteroid therapy^[1]^ for less than 3 months, as well as those who have been using a mouthwash in the past 3 months. Participants who have modifying factors for periodontal disease, such as diabetics, immunosuppressive smokers (cyclosporine), anticonvulsants (phenytoin), calcium channel blockers (nifedipine) and pregnant and lactating women as well as those who are HIV positive, or have Hepatitis B or C. Patients who require prophylactic antibiotic therapy for periodontal treatment who have had periodontal treatment in the last 6 months. Patients who have non-biofilm-induced gum disease.^[33]^ Patients who for some reason during the study have to initiate the use of the medicines and mouthwashes mentioned above or acquire a disease that is a modifying factor for periodontal disease or become pregnant. Patients who do not wish to remain part of the study may drop out whenever they wish.

### Researcher calibration

2.4

For calibration purposes one examiner will evaluate 5 patients with gingivitis, who will not be part of the study. Two complete periodontal exams (except third molars) per patient (with a 30-minute interval between them) will be performed at six sites per tooth, for clinical probing depth (PD), clinical level of insertion, PI and GI. The intra-examiner calibration will be repeated every 4 months. The intraclass correlation coefficient (ICC) will be calculated in order to evaluate the intra-examiner concordance ≥ 0.75 in relation to clinical periodontal parameters. The evaluation will be performed with periodontal probe marked in millimeters and this researcher will not be involved in the treatment of patients. This same examiner will be trained for biofilm and saliva collections for cytokine and microbiological analysis to maximize the reproducibility of the evaluations.

### Randomization

2.5

To randomly distribute the participants into the experimental groups, a 40-lot draw will be made using the Microsoft Excel program, version 2017. The distribution of groups will be identical (1: 1) for the two groups. The distribution will be done in a blocking fashion (8 groups of 5 patients). Opaque envelopes will be identified with sequential numbers (1 to 40) and there will be information about the corresponding experimental group in the order obtained in the draw. The envelopes will be sealed and will remain sealed in numerical order until the start of the periodontal treatments. The drawing and preparation of the envelopes will be performed by a person not involved in the study. Immediately prior to periodontal treatment the investigator responsible for treatment will open 1 envelope (without changing the numerical sequence) and perform the indicated procedure. Three additional patients will be included in each group in view of the dropout predicted in any clinical study (considering a dropout of 20%).

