### Study blinding

2.6

Only the researcher responsible for conducting the treatments (who will open the randomized envelopes) will know which treatment is assigned to each patient. The identification of each group will only be revealed by this researcher after statistical analysis of the data for all those involved in the study. Therefore, the researcher responsible for data collection, the microbiologist and the statistician will be blind regarding the treatments assigned to the groups. The patient will also be blind to the type of treatment performed, since the periodontal treatment will be identical in both groups and treatment with PDT will be simulated in the control group.

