#### Periodontal treatment

2.12.1

Participants in both (G1 and G2) groups will receive periodontal treatment (scaling and root planing - SRP) with universal curettes (Hu-Friedy) and ultrasound (Ultrassom Dabi Atlante - Profi Neo US, Ribeirão Preto, Brazil) depending on their needs. The SRP will be done in one session. Periodontal treatment will be performed by only one experienced researcher, who will not do the periodontal exams. Periodontal reassessment will be performed after 7 and 21 days. All patients in the control group will receive SRP, but will receive only a simulation of photodynamic therapy. To remove supragingival dental biofilm the Gracey Curette #3-4 will be used for the free surfaces of the anterior teeth and #7-8 on the free surfaces of the posterior teeth.

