#### Photodynamic therapy

2.12.2

Group 2 participants will receive PDT; the technique associates a photosensitive agent with a source of light and oxygen, in order to reduce the microbial load in places that are not accessible by curette.

After scaling, the procedures will be performed as described:

Application of methylene blue (0.005% - Chimiolux 5, DMC - purified water and methylene blue) with a carpule syringe and needle (with stop and without bevel) into the pseudopockets;Wait 1 minute (pre-irradiation time)^[35]^Irradiation with a red laser diode (λ = 660 nm) with an output power of 100mW (Therapy EC, DMC, São Paulo, SP, Brazil). The laser head will be positioned in direct contact with the pseudo periodontal pocket.^[36]^Apply at 8 sites where there is hyperplasia.Wash in abundance with saline solution until the photosensitizer is completely removed.During laser application both patient and operator will wear safety goggles.

Participants in G1 (Control- PDT placebo) will receive an agent with the same vehicle as that of the methylene blue to mimic irrigation with the photosensitizer; the laser will be switched off at the time of application.

PDT placebo procedures will be performed after scaling. The main difference between G1 and G2 is that in G1 the lase will be turned off but the same device will be positioned in the same way and with the same time of G2. Also, the beep sound will be recorded and turned on during application.

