For the treatment of gingivitis, the gold standard is usually scaling with a curette or ultrasound to remove biofilm.^[20]^ In this study, which considers the challenge of accessing difficult areas, such as in gingival hyperplasia, where the gum may cover the cervical base of the bracket and bands, photodynamic therapy was proposed as an adjuvant treatment, being appropriate for those areas where it is challenging for the curette to reach. The use of ultrasound was disregarded in this study, due to the possibility of bracket detachment with prolonged use, of ultrasound as shown by the Bonetti, 2014.^[10]^

The use of a photosensitizer associated with light at the appropriate wavelength was selected as the adjuvant therapy in this study because it is commonly understood that there is a need to decontaminate sites with gingivitis. PDT has been successfully used to treat periodontal diseases.^[22]^ The PDT ‘therapeutic window’ is effective in reducing the number of colonies or biofilm and may intensify the results of conventional mechanical treatments.^[25,31]^ In addition, while PDT is associated with coronary root scaling in this study, it has been shown to be effective as a primary therapy of choice in hard-to-reach areas, not just as adjunctive therapy.^[1]^

In Alvarenga's study, 2018^[35]^, a 50% attenuation of light at 3 mm from the laser probe was observed. The decrease in light, especially at deep sites where bacteria still remain viable, and the wide range of published results using fiber optics, convinced us to choose the trans-gingival method of application. In addition, a large amount of energy is lost as the fiber apparatus seal is still lacking.

Methylene blue is the most widely used PS in Brazil.^[27,28]^ It was chosen because it is already approved by ANVISA (the Brazilian Health Regulatory Agency), it is easily accessible in the market and it favors clinical applications, as the product is already designed for use in syringes.

Patients will be included according to Chapple, 2018,^[13]^ which characterizes gingivitis as when GI is greater than 10% and probing depth ≤ 3 mm from the distance of the Cemento-enamel Junction to the bottom of the pocket. Clinical signs of gingivitis inflammation will also be considered. Pseudo-pockets will be included in the study, and they will be preferred as choices as they are often areas difficult to access, where PDT can act very effectively.

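### The treating investigator opens the allocation envelope before scaling, although the first step that differs by arm comes only after scaling

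*Protocol article*

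**What the plan says.** Timing is stated three times in the protocol article, always the same way. Section 2.5 says "Immediately prior to periodontal treatment the investigator responsible for treatment will open 1 envelope (without changing the numerical sequence) and perform the indicated procedure", and that the sealed envelopes "will remain sealed in numerical order until the start of the periodontal treatments". Section 2.10 says "Immediately prior to periodontal treatment, the investigator will remove and open 1 envelope".

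Section 2.12.1 shows what periodontal treatment means: "Participants in both (G1 and G2) groups will receive periodontal treatment (scaling and root planing - SRP" in its abbreviation. It is done in one session with curettes and ultrasound, according to patient need. On the operator, the same section says "Periodontal treatment will be performed by only one experienced researcher, who will not do the periodontal exams".

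Section 2.12.2 places PDT after scaling in the experimental arm. For the control arm it says "PDT placebo procedures will be performed after scaling".

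Section 2.6 makes the treating researcher the only person who knows the assignment. The patient, the data collector, the microbiologist and the statistician are blind.

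**The concern.** Scaling is meant to be the same in both arms, so the operator does not need the assignment to perform it. Opening the envelope first means that the operator decides how thoroughly to scale, and with which instrument, while knowing whether PDT or a switched-off laser will follow. An operator could, without intending to, work harder in one arm, either to compensate control patients or to give the new therapy a good start.

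The primary variable, GI, is the percentage of bleeding sites over six sites per tooth, and the Discussion describes scaling as the usual gold standard for gingivitis. A systematic difference in scaling could therefore reach the primary comparison, and the analysis could not separate it from an effect of PDT.

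**Working it through.** The point concerns the order of procedures. The plan gives no figure to reproduce, so the check sets the sections side by side.

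**Order of events**

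| Step | Source | Differs by arm? |
|---|---|---|
| Baseline examination, questionnaire, saliva and biofilm samples | 2.7 | No |
| Oral hygiene guidance | 2.7, 2.11 | No |
| Envelope opened by the treating investigator | 2.5, 2.10 | Assignment becomes known |
| Scaling and root planing | 2.12.1 | No, by intention |
| PDT (G2) or simulated PDT (G1) | 2.12.2 | Yes, first such step |

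**Could periodontal treatment mean PDT?** No. Section 2.12.1 equates it with scaling and root planing in both groups, and Section 2.6 sets it apart from PDT in one sentence: "since the periodontal treatment will be identical in both groups and treatment with PDT will be simulated in the control group". The assignment is therefore known throughout scaling and first needed after it.

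**Does anything elsewhere repair this?** No section delays opening the envelope or gives scaling to a second, blinded operator. Section 2.12.1 assigns it to one researcher, and Section 2.6 identifies the person who conducts the treatments as the one who opens the envelopes.

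**Is there room for discretion?** Yes. Section 2.12.1 names curettes by tooth surface but leaves the use of curettes and ultrasound to patient need. It sets no duration or end point for scaling.

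**How much of the primary variable lies outside the PDT sites?** PDT is applied at 8 sites (2.10, 2.12.2), while GI counts six sites on every tooth (2.9). The number of teeth is not given. Assuming 24 to 28:

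- 24 × 6 = 144 sites, and 8 / 144 = 5.6%
- 28 × 6 = 168 sites, and 8 / 168 = 4.8%

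About 94% to 95% of the sites that make up GI thus receive no PDT. Scaling is not confined to those 8 sites, since Section 2.12.1 names curettes for both anterior and posterior teeth. This shows where a scaling difference could act, not how large it would be.

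**Illustration of consequence (all shifts assumed)**

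Inputs: 17 per arm (2.1, 2.10), Student's t test at 0.05 (2.15), two-sided by assumption, no true PDT effect, and a scaling-induced difference of b SD in GI between arms. The degrees of freedom are 2 × 17 − 2 = 32. The noncentrality is b × √(17/2) = 2.915 × b. The rejection rate is the probability that a noncentral t with 32 degrees of freedom falls outside ±c, where c is the 97.5th percentile of the central t.

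| Assumed b (SD) | Noncentrality | Two-sided rejection rate |
|---|---|---|
| 0 | 0 | 5.0% |
| 0.1 | 0.292 | 5.9% |
| 0.2 | 0.583 | 8.7% |
| 0.4 | 1.166 | 20.5% |

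The document supports no particular row. A shift in the other direction would instead tend to hide a real benefit of PDT.

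**The case against.** The safeguards in place are real. One experienced operator treats both arms in a single session and takes no outcome measurements. Baseline data are collected before treatment. The patient, examiner, microbiologist and statistician are blind. Instrument choice is tied to patient need, not to the operator's preference. No bias has been shown, and at small assumed shifts the error rate moves only modestly. All of this stands, and it limits the point to a risk. It does not remove that risk, because these measures protect how outcomes are measured and not how evenly scaling is delivered.

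Five stronger readings are tempting, and the document does not support them:

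- **Comparing an assumed GI shift with the effect size of 0.40.** Section 2.1 ties 0.40 to the amount of bacteria in crevicular fluid. No effect size or SD is given for GI, so such a ratio has no meaning here.
- **Saying that scaling produces most of the change in GI.** The Discussion calls it the gold standard, but nothing apportions the change among scaling, hygiene guidance and PDT.
- **Saying that Section 2.6 is undermined.** Its remark on identical periodontal treatment explains why the patient stays blind. A modest difference in scaling effort would not unblind a patient.
- **Treating the choice of the 8 sites as a second bias.** In the control arm the laser is off, so which sites receive the simulation should matter little for GI. In the experimental arm, choosing sites with hyperplasia is part of the intervention. Charting them before the envelope is opened is good order, not the repair of a demonstrated fault.
- **Using the conflict on ultrasound as evidence of performance bias.** That conflict exists whenever the envelope is opened, so it is a separate matter.

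**Conclusion.** The point holds as an avoidable risk of performance bias. Sections 2.5 and 2.10 disclose the arm to the operator before scaling, and Section 2.12.2 shows that it is first needed afterwards. The order is stated explicitly in two sections, so it is a fixed choice and not a detail lost in condensing the protocol.

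The size and direction of any bias cannot be estimated from the document, and the rates shown above rest on assumed shifts. No sample size, power or significance level changes. The operator must still know the arm for PDT or its simulation, so only the earlier exposure can be removed. Removing it also assumes that the operator cannot predict the next assignment from the earlier ones in a block.

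Separately, Section 2.12.1 includes ultrasound in the periodontal treatment, while the Discussion says "The use of ultrasound was disregarded in this study". The two statements contradict each other.

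**What to change.** In Sections 2.5 and 2.10, state that the next envelope is opened only after scaling is complete and the 8 sites for PDT or its simulation are charted, immediately before PDT or its simulation. Change the sentence in Section 2.5 on how long the envelopes stay sealed to match. The same person and the same envelopes can be used, with no extra visit or patient. The cost is a short pause within the session and a brief chart entry.

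As a separate correction, reconcile Section 2.12.1 with the Discussion on the use of ultrasound, so that the document gives one account of the instruments used in both arms.
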